### 7.1.3 Clinical

All eligible participants receiving any protocol defined treatment will be evaluated for clinical response to treatment as defined by the following measures.

- Disease-free survival (DFS), defined as the time from the date of randomization to the date of progression or death from any cause, whichever occurs first. A participant who dies without a reported progression will be considered an event on the date of death. Participants who have neither progressed nor died will be censored on the date of last evaluable tumor assessment.
- Overall survival (OS), defined as the time from the date of randomization to the date of death from any cause. Participants who do not experience an event (death) will be censored on the date of last follow-up/contact.

## 7.2 Sample Size and Accrual

Target sample size was based on the number of participants that could be accrued within the funding amount. This was set at 30 evaluable participants.

A primary endpoint for this study is a persistent response (pRsp) to vaccine antigens (see section 7.1.2). Results from Mel63 for the 38 evaluable participants treated on Arms C & D (6MHP + Montanide ISA-51 + polyICLC without & with mCy) resulted in 5 participants with a pRsp (13.1%). The 90% CI for this estimate is (5.3% to 25.7%) resulting in a half-width of 10.2%. For this study, an observed difference in the persistent response rates in the range of 28% to 31% (approximately 3 times the half-width) is needed to support that the addition of CDX-1127 to 6MHP vaccine warrants further study. This determination is based upon having positive lower and upper 90% CI bounds for the difference in pRsp for study Arm B – Arm A assuming Arm A pRsp rates of 13.1% to 25.7% using the score method of Miettinen and Nurminen.

Maximum target sample size is estimated to be 34 participants, which assumes a 10% dropout/ineligibility/lost to follow-up adjustment. Accrual is estimated at approximately 20 participants per year, therefore, accrual to the study should be completed in two years with final analysis occurring 9-12 months later.

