### **Accrual Goal**

Target accrual is estimated to be 30 eligible patients (15 per arm). Allowing for 10% ineligibility/dropout/lost-to-follow-up, up to 34 patients may be accrued.

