### 7.3 **Randomization**

Participants will be randomized 1:1 to treatment arms A and B with random block sizes of 2 and 4.

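### The go criterion for persistent response is given both as a 28% to 31% observed difference and as a confidence-interval rule; at 15 per arm the two conflict when the control arm has 0 or 1 responders

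*Combined protocol and SAP*

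**What the plan says.** Section 7.2 fixes the size by funding: "This was set at 30 evaluable participants". The synopsis (Accrual Goal) puts this at 15 per arm, and Section 7.3 states "Participants will be randomized 1:1 to treatment arms A and B with random block sizes of 2 and 4".

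The control assumption comes from "Results from Mel63 for the 38 evaluable participants treated on Arms C & D", of whom 5 had a persistent response (pRsp). Section 7.2 prints this as 13.1%, with a 90% CI of 5.3% to 25.7% and a half-width of 10.2%.

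The criterion for further study then appears in two forms. The first is a size: "an observed difference in the persistent response rates in the range of 28% to 31% (approximately 3 times the half-width) is needed". The second is the stated basis for it: "having positive lower and upper 90% CI bounds for the difference in pRsp", by the Miettinen-Nurminen score method, for control rates of 13.1% to 25.7%. The section does not mention whole-patient counts, does not say which form decides if they differ, and does not say what applies when the observed control rate is below 13.1%.

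**The concern.** A threshold in percent and a threshold on a confidence bound are interchangeable only near the control rates used to convert one into the other. The width of a score interval depends on the response rates, so a smaller difference suffices when few controls respond. With 15 per arm, 13.1% corresponds to about 2 control responders, and observing 0 or 1 is an ordinary outcome.

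What is at stake is the plan's one stated test of whether CDX-1127 goes forward on immunogenicity. If the two forms point in opposite directions, the choice between them would be made after the data are seen, in an open-label study.

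**Working it through.** **Inputs.** Historical pRsp 5/38; control rates 13.1% and 25.7%; 90% two-sided Miettinen-Nurminen interval (all Section 7.2); 15 per arm (synopsis).

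**The plan's supporting figures.** 5/38 = 13.16%. The Clopper-Pearson 90% CI is 5.33% to 25.70%. The half-width is (25.70 − 5.33)/2 = 10.18, and 3 × 10.18 = 30.5. These reproduce.

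**The rule as a formula.** The lower 90% bound exceeds 0 when the score statistic at zero difference exceeds 1.645. At zero difference the restricted estimates both equal the pooled rate p. With N = 30 and the N/(N−1) factor, the variance multiplier is (2/15) × (30/29) = 4/29, so

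Z = d / √[p(1 − p) × 4/29], with d the observed difference.

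**The printed range, rates treated as continuous.**
- Control 13.1%, d = 0.2699: p = 0.266, Z = 0.2699/0.1641 = 1.645. Threshold 27.0%.
- Control 25.7%, d = 0.3001: p = 0.407, Z = 0.3001/0.1825 = 1.645. Threshold 30.0%.

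The printed 28% and 31% each lie about one point above these values. In whole percents they are the first with a clearly positive lower bound: +0.89 points at 28% (control 13.1%) and +0.94 at 31% (control 25.7%). The bound is +0.01 at 27% and −0.01 at 30%, respectively.

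**Whole patients, 15 v 15.** Differences are multiples of 1/15 = 6.67 points, so 4/15 = 26.7% is followed by 5/15 = 33.3%.

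| Control responders | Largest failing count (d, Z, lower bound) | Smallest passing count (d, Z, lower bound) |
|---|---|---|
| 0 | 2 (13.3%, 1.44, −3.5) | 3 (20.0%, 1.80, +2.7) |
| 1 | 4 (20.0%, 1.45, −3.2) | 5 (26.7%, 1.80, +2.5) |
| 2 | 6 (26.7%, 1.62, −0.4) | 7 (33.3%, 1.96, +5.6) |
| 3 | 7 (26.7%, 1.52, −2.2) | 8 (33.3%, 1.86, +4.0) |
| 4 | 8 (26.7%, 1.47, −3.3) | 9 (33.3%, 1.81, +3.1) |

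Lower bounds are in percentage points. Because nothing is attainable between 26.7% and 33.3%, using 28% or 31% as the cut-off gives identical decisions.

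**Where the forms disagree.** With 2, 3 or 4 control responders both require 33.3%. With 0 or 1, the results 3 v 0, 4 v 0 and 5 v 1 pass the interval rule but are below 28%. (The mirror images 15 v 12, 15 v 11 and 14 v 10 also disagree, but add nothing visible at the rates below.)

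**How often.** For each pair the probability is Bin(t; 15, treated rate) × Bin(c; 15, control rate). Treated rates are assumptions; 41.1% and 56.7% are 13.1 + 28 and 25.7 + 31.

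| Control v treated | 3 v 0 | 4 v 0 | 5 v 1 | Total |
|---|---|---|---|---|
| 13.1% v 13.1% | 2.31% | 1.04% | 0.78% | about 4% |
| 13.1% v 30% | 2.07% | 2.66% | 5.67% | about 10% |
| 13.1% v 41.1% | 0.67% | 1.40% | 4.87% | about 7% |
| 5.3% v 33.3% | 5.76% | 8.62% | 7.95% | about 22% |
| 25.7% v 56.7% | 0.00% | 0.02% | 0.25% | about 0.3% |

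Summing over all outcomes, the chance of a go at 13.1% v 30% is 28.9% under the interval rule and 18.5% under the printed threshold. At 5.3% v 33.3% it is 66% v 44%.

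**The case against.** The strongest reply is that the percentage range is derived from the interval rule, for stated control rates, and is accurate to about a point. That stands. A reader might infer that 28% to 31% is an arithmetic error, or that the true hurdle at the assumed rates is higher than printed. The documents support neither: the range reproduces on a continuous scale, and with 2 to 4 control responders the first attainable difference at or above 28% is the same 33.3% that the interval rule requires.

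A reader might also infer that a difference of 28% to 31% can never be observed. That holds only for an exact 15/15 evaluable split, which is a target and not guaranteed: up to 34 may be accrued, and evaluability is settled after randomization. With other splits (treated/control) such values do occur, for example 6/14 v 2/16 = 30.4%, 7/16 v 2/15 = 30.4% and 7/17 v 2/17 = 29.4%, and all three pass the interval rule.

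Section 7.5 adds that the study estimates differences and makes no statistical comparisons, so no formal error rate depends on this. True, but Section 7.2 still names a result that is needed before further study, and that result should have one meaning. It can also be said that the interval rule is already given as the basis. That points to the sensible resolution, but the text does not say that it overrides the percentage.

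**Conclusion.** The point holds as a conflict between two statements of one criterion, confined to low control counts. At 15 v 15 the forms part at 3 v 0, 4 v 0 and 5 v 1; at 2 to 4 control responders they agree. At a control rate of 13.1% they disagree in about 4% to 10% of trials over treated rates of 13.1%, 30% and 41.1%. Disagreement rises to about 22% at 5.3% v 33.3%, where 5.3% is the plan's own lower limit for the historical rate, and falls to about 0.3% at 25.7% v 56.7%.

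The chance of 0 or 1 control responders at 13.1% is about 40%. That should not be read as the chance of conflict, since most results with so few control responders fail both forms or pass both.

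The counts assume exactly 15 evaluable per arm and the N/(N−1) factor. The entry for 2 control responders is sensitive to that factor: without it, 6 v 2 has a lower bound of +0.1 points and would pass. It should be corrected because it is a stated decision threshold and the correction is nearly free.

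**What to change.** In Section 7.2, state that the go rule is a lower 90% Miettinen-Nurminen bound (with the N/(N−1) factor) above 0 for the CDX-1127 arm minus the vaccine-alone arm. Then either label 28% to 31% as an approximation for control rates of 13.1% to 25.7%, or replace it with the smallest passing counts at 15 per arm: 3 v 0, 5 v 1, 7 v 2, 8 v 3 and 9 v 4. Say that the counts will be recomputed for the actual evaluable numbers.

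Reconcile the arm labels in the same sentence. Section 7.2 takes the difference as Arm B minus Arm A and gives Arm A the control rates, whereas Table 9 makes Arm A the CDX-1127 arm.

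The cost is a sentence and, if counts are used, a five-line table. The sample size and the analysis method are unchanged.

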#### 5.3.1 Overview

Subjects in Arm A will receive three doses of CDX-1127(3 mg/kg)

- Day 1
- Day 36
- Day 78

The study drug will be administered intravenously over a 90-minute time period.

CDX-1127 will be administered as an intravenous infusion in accordance with the applicable study protocol. CDX-1127 should not be administered as a bolus injection.

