## 7.0 **STATISTICAL CONSIDERATIONS**

This is an early phase randomized trial to obtain preliminary data on the safety and immunogenicity of CDX-1127 (CD27 antibody) administered concurrently with a melanoma vaccine (6MHP). The primary goals are to assess the safety of CDX-1127 when administered with vaccine; and to obtain preliminary estimates of the difference in immune outcome measures between participants randomized to 6MHP + CDX-1127 (Arm A) versus 6MHP (Arm B). Exploratory goals are to obtain preliminary data on the induction of antibodies; CD8+ T cell response to antigens; cell activation and exhaustion; and clinical outcomes. Eligible participants will be accrued and randomized with equal allocation to one of two treatment arms as shown in [Table 9](#).

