**Table 9: Arms**

|                                                                    |
|--------------------------------------------------------------------|
| A: 6MHP + Montanide ISA-51 + polyICLC + CDX-1127 (6MHP + CDX-1127) |
| B: 6MHP + Montanide ISA-51 + polyICLC (6MHP)                       |

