### 7.5 **Analyses**

Study populations and evaluation criteria are noted in [Section 7.1](#). Adverse events will be summarized by frequency and magnitude of event. Incidence of DLTs will be monitored against the safety bounds above. The bounds are non-binding, and provide a guideline that may result in study modification or closure.

A 5-fold or greater CD4+ Th1 memory response to vaccine antigens compared to baseline is consider a response. Amounts less than 5-fold are considered as a non-response. Immune and clinical endpoints are defined in [Section 7.1.2](#) and in [Section 7.1.3](#), respectively. Time to event measures (DFS and OS) will be estimated by the methods of Kaplan and Meier.

This study is designed to estimate differences and not to make statistical comparisons between arms. All CD4+ T cell and CD8+ T cell ELISpot results will be assessed relative to the participant specific baseline measure with graphical representation of measures over time. The difference in the proportion of participants considered to have a durable response between arms will be estimated and a 90% confidence interval around the difference, using the score method of Miettinen and Nurminen. Similarly, the difference in

the proportion of participants considered to have a memory response at day 183 between arms will be estimated and a 90% confidence interval around the difference calculated. In addition, repeated measure models will be explored to estimate difference in patterns of response between arms over time for CD4+ T cell, CD8+ T cell and percent of circulating Tregs (with a log10 transformation). Within an arm, for each participant, the difference in amount of FoxP3+ cells in the vaccine site microenvironment at weeks 3 and 12 (for those with biopsies done on week 12) will be calculated. Estimated difference in mean change by arm with 90% CI estimates around the difference in means will be used to estimate potential differences by arm.

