| 02-05-24     | 1. Arm assignments in Table 9 within Section 7 were corrected to be consistent with the arm assignments described throughout the protocol (Arm A: 6MHP + CDX-1127; Arm B: 6MHP only). Text in Section 7.0 was revised to clarify which group received which treatment for consistency.                                                                                                                                                                                                                                                                                                                                                                                                                                                                                                                                                                                                                                                                                                                                                                                                                                                                                                                                                                                                                                    |

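### The pRsp criterion in Section 7.2 subtracts Arm B – Arm A, so under the plan's own arm labels CDX-1127 is supported only if vaccine alone does better

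*Combined protocol and SAP*

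**What the plan says.** The arm definitions agree with one another:

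- Table 9 defines one arm as "A: 6MHP + Montanide ISA-51 + polyICLC + CDX-1127 (6MHP + CDX-1127" and the other as "B: 6MHP + Montanide ISA-51 + polyICLC (6MHP".
- Section 7.0 describes "participants randomized to 6MHP + CDX-1127 (Arm A) versus 6MHP (Arm B".
- Section 5.3.1 says "Subjects in Arm A will receive three doses of CDX-1127(3 mg/kg".
- Table 7, footnote c, restricts varlilumab to Arm A, and the two calendars in Section 9.1 follow the same labels.

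Section 7.2 takes the historical persistent response rate (pRsp) from Mel63 Arms C and D: 5 of 38, or 13.1%, with 90% CI 5.3% to 25.7%. Those patients had vaccine plus polyICLC, without or with mCy, and no CDX-1127. It then says that an observed difference of 28% to 31% "is needed to support that the addition of CDX-1127 to 6MHP vaccine warrants further study". The basis is that both limits of a 90% Miettinen-Nurminen interval are positive, with "bounds for the difference in pRsp for study Arm B – Arm A assuming Arm A pRsp rates of 13.1% to 25.7" per cent.

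Section 7.5 gives an interval for a different endpoint: "The difference in the proportion of participants considered to have a durable response between arms will be estimated and a 90% confidence interval". It adds one for memory response at day 183. It does not mention pRsp or give an order of subtraction.

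**The concern.** The sentence in 7.2 treats Arm A as the vaccine-only reference and Arm B as the arm with CDX-1127, the reverse of every arm definition in the plan. Under the defined labels, both limits of B – A can be positive only when vaccine alone has the higher pRsp rate. Taken literally, a benefit of CDX-1127 counts against it and a detriment counts as support.

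No other passage settles the direction. Persistent response is the primary immunogenicity endpoint (Section 2.1). The durable and memory responses covered in 7.5 are secondary (Section 2.2). Section 7.1.2 defines a persistent response as a durable response plus a response on day 127 or 176, so the durable-response interval cannot stand in for it. Section 7.2 alone states the sign, the reference arm and the success criterion for this comparison.

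The change log suggests why the sentence was missed. Its latest entry says "Arm assignments in Table 9 within Section 7 were corrected to be consistent with the arm assignments described throughout the protocol" and lists the text of 7.0 as revised, but not 7.2. That is context only; the contradiction lies within the current text.

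**Working it through.** **Inputs.** From 7.2: 5/38 historical responders, reference rates 13.1% and 25.7%, threshold 28% to 31%, 90% Miettinen-Nurminen interval, 30 evaluable participants. From 7.3: 1:1 allocation, hence 15 per arm.

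**1. Historical rate.** 5/38 = 13.16%. The exact (Clopper-Pearson) 90% CI is 5.33% to 25.70%, and the half-width is (25.70 – 5.33)/2 = 10.18 points. These match 7.2.

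**2. The 28% to 31% threshold.** The Miettinen-Nurminen lower limit exceeds zero when the score statistic at zero difference exceeds 1.645. At zero difference the constrained estimate is the pooled proportion p, so with n per arm

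z = d / √[ p(1 – p) × (2/n) × 2n/(2n – 1) ].

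For n = 15 the multiplier of p(1 – p) is (2/15) × (30/29) = 0.1379.

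| Reference rate | d | p | z |
|---|---|---|---|
| 13.1% | 0.27 | 0.266 | 0.27/0.1641 = 1.645 |
| 13.1% | 0.28 | 0.271 | 0.28/0.1651 = 1.696 |
| 25.7% | 0.30 | 0.407 | 0.30/0.1825 = 1.644 |
| 25.7% | 0.31 | 0.412 | 0.31/0.1828 = 1.696 |

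The lower limit crosses zero at 27.0 and 30.0 points, within about a point of the plan's range. With 14 per arm it crosses at 28.2 and 31.2. So the plan's figure is reproduced with the 13.1% to 25.7% arm as the lower, subtracted arm. Because that rate comes from patients without CDX-1127, the subtracted arm has to be vaccine alone, which is Arm B.

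**3. Same data, both directions, 15 per arm.** Here CDX-1127 (Arm A) is the better arm.

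| Arm B rate, Arm A rate | A – B, 90% CI | B – A as written, 90% CI |
|---|---|---|
| 13.1%, 41.1% | +0.9% to +52.1% | –52.1% to –0.9% |
| 25.7%, 56.7% | +0.9% to +56.0% | –56.0% to –0.9% |
| 2/15, 7/15 | +5.6% to +57.0% | –57.0% to –5.6% |

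For the last row, p = 9/30 = 0.30 and z = 0.3333/√(0.21 × 0.1379) = 0.3333/0.1702 = 1.96, which exceeds 1.645. In whole patients, 2, 3 or 4 responders on vaccine alone need 7, 8 or 9 on the other arm, a difference of 5/15 = 33.3% each time.

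**4. Probability of meeting the criterion.** This is the sum of Bin(a; 15, p_A) × Bin(b; 15, p_B) over all outcomes for which the relevant lower limit is above zero.

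| True rate, Arm B | True rate, Arm A | A – B | B – A as written |
|---|---|---|---|
| 13.1% | 41.1% | 0.52 | 0.0003 |
| 25.7% | 56.7% | 0.53 | 0.0003 |
| 13.1% | 13.1% | 0.049 | 0.049 |
| 25.7% | 25.7% | 0.045 | 0.045 |

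By symmetry, if vaccine alone were truly the better arm by 28 or 31 points from these reference rates, the written criterion would be met with probability 0.52 or 0.53.

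**5. Sample size.** 30/0.9 = 33.3, rounded up to 34, as in 7.2. The direction of subtraction does not enter it.

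**The case against.** The best defence is that the intended direction can be recovered. The preceding sentence in 7.2 names the addition of CDX-1127 as the thing to be supported, the reference rate comes from patients who never received it, and the objective is framed as improvement. On this view there is one transposition of labels, and A – B and B – A give mirror-image intervals of the same width. The sentence sits in a sample-size section for a trial whose size was set by funding. Section 7.5 says the study is for estimation and not for statistical comparison. In an open-label trial, a wrong conclusion would need an analyst to overlook the treatment names.

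Much of this stands. The intent can be inferred, one swap explains both reversed labels, no number in the plan changes, and the criterion is not a formal test. No stopping, dosing or randomisation rule depends on it. The omission of pRsp from 7.5 is a separate gap; its relevance here is that nothing there corrects or overrides 7.2.

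The defence does not make the text right. Section 7.2 says what result is needed to support further study, and it is the only place where that is said for the primary immunogenicity endpoint. A prespecified criterion should give the right answer when followed as written, without the reader having to infer that its labels are reversed.

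**Conclusion.** The point holds and should be corrected before the analysis. Under the plan's own arm definitions, the criterion for the primary pRsp comparison has the wrong sign and assigns the historical rate to the wrong arm. The effect is a complete reversal: results that should support CDX-1127 fail, and results that favour vaccine alone pass. The thresholds, interval width, sample size and dropout allowance are unaffected.

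This rests on the current arm definitions in 5.3.1, 7.0, Table 9 and the calendars. The intervals and probabilities assume 15 evaluable participants per arm, and the 7/15 against 2/15 counts are an illustration, not trial data. The direction error depends on neither.

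**What to change.** - **Section 7.2:** define the difference as Arm A minus Arm B, and assign the 13.1% to 25.7% reference rates to Arm B. Naming the treatments beside the letters would prevent a repeat.
- **Section 7.5:** state the Arm A minus Arm B difference in pRsp, with its 90% Miettinen-Nurminen interval, as the primary immunogenicity estimate. Keep durable and memory response as secondary, in the same direction.
- **Precaution:** before analysis, confirm that any programs and table shells use the Table 9 labels, and that the arm-specific DLT counts in Section 1.1 do too. Nothing in the documents shows an error in either.

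The cost is two sentences of protocol wording and a label check. There is no effect on participants, thresholds or sample size.

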### 7.3 **Randomization**

Participants will be randomized 1:1 to treatment arms A and B with random block sizes of 2 and 4.

### 7.4 **Safety Monitoring**

Toxicities will be monitored using CTCAE 5.0 criteria, with additional recording of immune-related adverse events (irAE). Stopping rules will be based on expected DLT rates discussed in [Section 7.1.1](#) for each of the combination arms. Significant increases over the reported rates are not expected but would be a reason for early discontinuation. Thus, formal safety bounds based upon the observed number of participants who experience a DLT as defined in [Section 8.9](#) will guide decisions about early stopping due to potential safety concerns. If a stopping bound is crossed then accrual to the study will be suspended until the study PI, co-investigators, sponsors and the DSMC can review the data, and determine if the study should continue, be amended or be closed to further accrual. The rate of DLTs will be monitored up to 30 days after the last vaccination. A sequential probability ratio test (SPRT) based upon a binomial test of proportions for DLTs will be used. Only the upper boundary will be used for monitoring to protect against excessive failure rates. The stopping boundary are for a SPRT contrasting a 5% versus 25% DLT rate, with nominal type I and II errors of 10% and 10%, respectively.

Stopping guidelines have triggered two study reviews and amendments. Upon approval of treatment change in Protocol v12-03-2020, the monitoring stopping guidelines will be applied separately to the subset of participant's accrued pre and post approval of Protocol v12-03-2020.

| Table 10: Stopping Guidelines for DLTs                        |          |
|----------------------------------------------------------------------|----------|
| Number of participants pre and post approval of Protocol v12-03-2020 | Boundary |
| 2-6                                                                  | $\geq 2$ |
| 7-14                                                                 | $\geq 3$ |
| 15-16                                                                | $\geq 4$ |

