### 5.5 Dose Delays

#### 5.5.1 Dose Delays Due to Toxicity

- Dose delays for vaccines and CDX-1127

In circumstances where assessment of an AE is limited, such as by intercurrent illness, or when laboratory studies are required to assess for other causes of toxicity, the vaccine\* and/or CDX-1127 schedule may be interrupted for up to 21 days.

- If a toxicity can be clearly attributed to either the vaccine or CDX-1127, then only the investigational drug that caused the toxicity will be delayed.
- One vaccine and/or one CDX-1127 delay up to 21 days is allowed if due to an AE, regardless of attribution.
- If there is more than one vaccine and/or one CDX-1127 delay by 7 days or more due to an AE, regardless of attribution, the investigational drug that caused the toxicity should be discontinued. The remaining investigational drug may be continued.
- Missed doses may be shifted. Participants who are treated outside of the established schedule should return to the original schedule as soon as possible, keeping in mind that there must be at least a minimum of 6 days in between CDX-1127 infusions and a minimum of 5 days in between vaccines.

\*The vaccine includes all components that make up the vaccine (e.g.6MHP + Montanide ISA-51 with or without).

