|                                                      | ± 15 or more days                | Labs                                                                                                  | Yes                       |
| Vaccine 5                                     |                                  |                                                                                                       |                           |
| Day 57                                               | ± 7 days                         | Vaccine/Labs before Protocol v12-03-2020.
Labs only after approval of Protocol v12-03-2020.        | No                        |
|                                                      | ± 8 to 14 days                   | Vaccine/Labs before Protocol v12-03-2020.
Labs only after approval of Protocol v12-03-2020.        | Yes                       |
|                                                      | ± 15 or more days                | Labs                                                                                                  | Yes                       |
| Vaccine 6/Varlic                   |                                  |                                                                                                       |                           |
| Day 78                                               | ± 7 days                         | Vaccine/Varli/Labs before Protocol v12-03-2020.
Varli/Labs after approval of Protocol v12-03-2020. | No                        |
|                                                      | ± 8 to 14 days                   | Vaccine/Varli/Labs before Protocol v12-03-2020.
Varli/Labs after approval of Protocol v12-03-2020. | Yes                       |
|                                                      | ± 15 or more days                | Labs                                                                                                  | Yes                       |
| Assessment/Biopsy                             |                                  |                                                                                                       |                           |
| Week 12 (day 85)                                     | ± 7 days                         | Labs/Biopsy/Scans before Protocol v12-03-2020.                                                        | No                        |

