### **5.13 Biopsies**

#### Vaccine Site Biopsies

Before Protocol v12-03-2020, each participant had a biopsy of a vaccine site at two time points (days 22 and 85 or End of Treatment). After approval of Protocol v12-03-2020, only the biopsy at day 22 will be done. The biopsy will consist of three 4-mm punch biopsies of skin.

Prior to Protocol v12-03-2020, the vaccine site biopsy at day 85 was required for all participants, except that it was optional for participants who discontinued vaccine therapy before vaccine 6 but did not discontinue varilumab therapy if applicable, and it should not have been done if the participant had ulceration at the vaccine site or had a vaccine-site related DLT.

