#### 8.4.2 Time Span for Reporting Adverse Events

Reporting of AEs will begin when the participant is first administered the study drug or has a study related procedure. Events occurring through 30 days after administration of the last dose of vaccine or varlilumab, regardless of attribution, will be reported. Participants are to be contacted 30 days after receiving study drug to obtain adverse event data. This may be done by phone, mail, email, or in person. For patients who discontinue protocol therapy prior to day 176, they should be contacted 30 days after the last vaccine or varlilumab administration for completion of AE data collection.

AEs should be followed to resolution or stabilization. If an AE worsens and becomes an SAE, it should be reported as serious per the guidelines specified for SAE reporting.

AEs that are possibly, probably, or definitely related to any of the study drugs will be recorded until the participant completes treatment follow-up. If, during treatment follow-up, the participant receives an alternative anti-cancer treatment, participants will be off treatment follow-up and will be followed yearly for disease progression and survival.

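### The Table 10 DLT count closes 30 days after the last vaccination, so on a literal reading some Arm A DLTs after a later varlilumab infusion are collected but not counted

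*Combined protocol and SAP*

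**What the plan says.** Section 7.4 bases the safety guideline on "formal safety bounds based upon the observed number of participants who experience a DLT". It uses the upper limit of a sequential probability ratio test "contrasting a 5% versus 25% DLT rate, with nominal type I and II errors of 10% and 10%, respectively". On timing it says: "The rate of DLTs will be monitored up to 30 days after the last vaccination". Varlilumab is not mentioned in that sentence.

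Section 8.4.2 has a wider window for collection: "Events occurring through 30 days after administration of the last dose of vaccine or varlilumab, regardless of attribution, will be reported".

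The two windows can separate because the two drugs can stop at different times. Section 5.5.1, on stopping a drug after repeated toxicity delays, adds: "The remaining investigational drug may be continued". Section 5.13 describes participants who "discontinued vaccine therapy before vaccine 6 but did not discontinue varilumab therapy if applicable"; footnote l of the Arm A calendar (9.1) does the same, and the EOT 1 visit in 9.1 provides for stopping a single drug. Section 5.3.1 schedules varlilumab in Arm A on days 1, 36 and 78. Under the amended schedule in 5.2.1, vaccine is given on days 1, 8, 15 and 36, with a booster on day 176. Table 7 accordingly lists the day 78 visit as "Varli/Labs after approval of Protocol v12-03-2020".

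**The concern.** Safety of adding CDX-1127 (varlilumab) is the first primary objective, yet the window for counting DLTs against the stopping guideline is timed from the background vaccine, which both arms receive. In Arm B vaccine is the only study drug, so 7.4 and 8.4.2 give the same 30 days. In Arm A they can differ, and what falls between them is follow-up after an infusion of the drug under test.

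The amendment made this more likely. On the initial schedule the sixth vaccine and the third infusion shared day 78, so a window timed from that vaccine also covered that infusion. Vaccine was then removed from day 78. Section 7.4 was revised to apply the bounds separately before and after the amendment, but its window is still tied to vaccination only.

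At stake is whether a given participant adds to a count that triggers review at 2, 3 or 4. The guideline is in active use: 7.4 records that it has already led to two reviews and amendments.

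**Working it through.** **Plan's own figure.** Inputs from 7.4: p0 = 0.05, p1 = 0.25, α = β = 0.10, upper limit only. The Wald upper limit for n participants is

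x ≥ [ln((1−β)/α) + n·ln((1−p0)/(1−p1))] / [ln(p1/p0) + ln((1−p0)/(1−p1))].

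- ln(0.90/0.10) = 2.197; ln(0.95/0.75) = 0.2364; ln(0.25/0.05) = 1.609; denominator 1.609 + 0.2364 = 1.846.
- The limit is 2.197/1.846 + n·(0.2364/1.846) = 1.190 + 0.1281n, rounded up.
- n = 2 gives 1.45 and n = 6 gives 1.96, so 2. n = 7 gives 2.09 and n = 14 gives 2.98, so 3. n = 15 gives 3.11 and n = 16 gives 3.24, so 4.

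This matches Table 10 exactly. The boundaries are sound; the question is only which participants enter x.

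**Window arithmetic.** Window end under 7.4 = day of last vaccine + 30. Days counted after an infusion = window end − infusion day, between 0 and 30. Scheduled days are used.

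| Last vaccine given | 7.4 window ends | Counted after day 36 infusion | Counted after day 78 infusion |
|---|---|---|---|
| Day 1 | 31 | 0 of 30 | 0 of 30 |
| Day 8 | 38 | 2 of 30 | 0 of 30 |
| Day 15 | 45 | 9 of 30 | 0 of 30 |
| Day 36 | 66 | 30 of 30 | 0 of 30 (closed 12 days earlier) |
| Day 57 (initial schedule) | 87 | 30 of 30 | 9 of 30 |
| Day 78 (initial schedule) | 108 | 30 of 30 | 30 of 30 |
| Day 176 booster | 206 | 30 of 30 | 30 of 30 |

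Under 8.4.2, a participant whose final study drug is the day 78 infusion is covered to 78 + 30 = day 108, whenever vaccine stopped.

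**Who falls in the gap.**
1. Arm A participants who stop vaccine for a non-DLT reason and continue varlilumab. A vaccine DLT is not the issue: it ends protocol treatment (5.6), and that participant is already counted.
2. On the amended schedule, on-schedule Arm A participants with a first DLT after the day 78 infusion, say on day 85. The DLT ends treatment under 5.6, the booster is not given, the last vaccination remains day 36, and the literal window closed on day 66.

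**Sensitivity.** The documents give no number affected, so the missed share m below is an assumption. It is the fraction of all DLTs in the monitored group that go uncounted. With a true rate of 25%, the counted rate is 0.25(1 − m). The exact probability of crossing Table 10 by n = 16, by recursion over the binomial path, is:

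| m | Counted rate | Probability of crossing |
|---|---|---|
| 0 | 0.250 | 0.76 |
| 0.10 | 0.225 | 0.69 |
| 0.20 | 0.200 | 0.60 |
| 0.30 | 0.175 | 0.51 |

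At a true rate of 5% with none missed it is 0.05. These figures show how sensitive the guideline is to missed events; they do not estimate what happens in this trial.

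**The case against.** The strongest reply is that the last scheduled vaccination is the day 176 booster. Read prospectively, an on-schedule participant at day 78 has not had the last vaccination, and the window is still open. That reading is possible, and for anyone who receives the booster the gap disappears. But 7.4 does not say whether it means the last scheduled or the last received vaccination. The prospective reading also does not clearly help someone who has permanently stopped vaccine.

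The first group is also narrow. It needs a non-DLT reason for stopping vaccine, continued varlilumab, and then a first DLT outside the window. Footnote a of Table 7 narrows it further, because repeated vaccine delays for non-toxicity reasons take a participant off protocol treatment altogether. The 5.13 text concerns a biopsy that has since been removed, so 5.5.1 and EOT 1 are the better support. All of this limits frequency; none of it closes the gap.

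A reader might infer that the primary DLT endpoint is biased downward in Arm A. The documents do not support that. The endpoint in 2.1 has no time limit, the DLT definition in 8.9 has no window and describes monitoring as continuous, and 7.5 sets no cut-off for the safety summary. The 30-day sentence belongs to the accrual guideline alone.

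A reader might also infer that a safety hold would be delayed in practice. That is not shown either. DLTs go to the coordinating center within 24 hours and on to the manufacturer within 24 hours (8.6.1, 8.6.5). Related events are recorded until treatment follow-up ends (8.4.2). The DSMC meets monthly and reviews all adverse events and the application of the stopping rules (8.13.1). The bounds are non-binding (7.5), and the study can be suspended for unacceptable risk whatever the count (8.15). What remains open is whether such an event formally adds to Table 10.

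**Conclusion.** The inconsistency is real and confined to the stopping guideline. On the literal wording of 7.4, a first DLT after the day 78 infusion is not counted when the last vaccine was day 36 or earlier. When the last vaccine was day 15, 21 of the 30 days after the day 36 infusion (30 − 9) are also not counted. On the amended schedule this extends to on-schedule Arm A participants whose DLT prevents the booster.

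The conclusion rests on scheduled visit days and on reading the last vaccination as the last one received. The number affected cannot be derived from the documents. With boundaries of 2, 3 or 4 participants one event can matter, but reporting duties, DSMC review and non-binding bounds limit the practical harm. It should be corrected because the count is ambiguous for the drug under test. It is not evidence of a biased safety result.

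**What to change.** Reconcile 7.4 with 8.4.2 so that both use one window. In 7.4, replace the timing sentence with wording such as: *a participant's DLT counts toward Table 10 if it occurs no later than 30 days after that participant's final administration of vaccine or varlilumab, whichever came later.* Referring to administrations actually received also removes the ambiguity about the booster.

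The cost is one sentence. Table 10 does not change, because its limits depend on the two rates and the two error levels and not on the length of the window. No new data are needed, since 8.4.2 already collects the events. Section 7.5 needs no edit on this ground, as it contains no cut-off.
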